## 8.3. TRIAL DEVELOPMENT

After accepting the participation, patients would be assessed the first visit. Study visits would be at entry (BL) and weeks 4, 12, 24, 36 and 48.

Plasma samples will be stored at –80ºC.

Viral load, complete blood count, CD4 cells count, and a complete biochemistry and haematology will be performed at every visit (except for week 4 where only CD4 count and viral load will be performed).

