# 1.- SUMMARY

## 1.0. TYPE OF APPLICATION

Clinical trial including a marketed investigational product under different conditions from the authorised.

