## 7.5. CONCOMITANT TREATMENTS

All other treatments apart from antiretroviral medication administered during the study period will be considered concomitant treatments and should be documented in the CRF.

It is remembered that the patients who participate in the study should not continue any concomitant treatment without the knowledge and permission of the investigator.

Following known interactions with medicinal products are listed:

| **Medicinal product** | **Clinical comment** |
| --- | --- |
| Digoxin | It is recommended that digoxin levels be monitored when digoxin is combined with etravirine. |
| Amiodarone  Bepridil  Disopyramide  Flecainide  Lidocaine (systemic)  Mexiletine  Propafenone  Quinidine | Caution is warranted and therapeutic concentration monitoring, if available, is recommended for antiarrhythmics when co-administered with etravirine. |
| Clarithromycin | Alternatives to clarithromycin should be considered for the treatment of *Mycobacterium avium* omplex. |
| Warfarin | It is recommended that the international normalised ratio (INR) be monitored when warfarin is combined with etravirine. |
| Rifampicin  Rifapentine | Combination not recommended. |
| Rifabutin | The combination of etravirine and rifabutin should be used with caution due to the risk of decrease in etravirine and rifabutin exposures. |
| Diazepam | Alternatives to diazepam should be considered. |
| Dexamethasone (systemic) | Systemic dexamethasone should be used with caution or alternatives should be considered, particularly for chronic use. |
| St John's wort *(Hypericum perforatum)* | Combination not recommended. |
| Atorvastatin | The combination of etravirine and atorvastatin  can be given without any dose adjustments, however, the dose of atorvastatin may need to be altered based on clinical response. |
| Fluvastatin  Lovastatin  Pravastatin  Rosuvastatin  Simvastatin | Dose adjustments for these HMG Co-A reductase inhibitors may be necessary. |
| Cyclosporine  Sirolimus  Tacrolimus | Co-administration with systemic immunosuppressants should be done with caution because plasma concentrations of cyclosporine, sirolimus or tacrolimus may be affected when co-administered with etravirine. |
| Sildenafil  Vardenafil  Tadalafil | Concomitant use of PDE-5 inhibitors with etravirine may require dose adjustment of the PDE-5 inhibitor to attain the desired clinical effect. |

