**Secondary objectives:**

To compare the immunological efficacy of etravirine-based regimen with standard PI-containing regimens.

- Changes in CD4+/CD8+ T lymphocytes at week 48 from baseline.

To compare the tolerability and toxicity of etravirine-based regimen with standard PI-containing regimens.

- Changes in lipid parameters (total, HDL-, LDL-cholesterol and triglyceride levels) at week 48 relative to baseline values.
- Changes in the administration of lipid-lowering drugs throughout the study (new administrations or the withdrawal of previous lipid-lowering drugs).
- Percentage of patients who withdraw from the study.
- Percentage of patients who withdraw from the study due to toxicity.
- Percentage of patients with toxicity ≥ grade 3.

To compare the cardiovascular risk of etravirine-based regimen with standard PI-containing regimens.

- Changes in cardiovascular risk estimated by changes in the SCORE equation at week 48 relative to baseline values.

To compare patient’s satisfaction of etravirine-based regimen with standard PI-containing regimens.

- Changes in patient’s satisfaction at week 48 from baseline, using a 100 mm analogue visual scale.

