### 8.2.2. Laboratory Test

Patients will fast for at least 8 hours prior to assessment, in the points specified in the flow chart of the study (section 8.3). The following parameters will be quantified, as needed:

- **Haematology:**

Leucocyte Hemoglobin

Lymphocyte count Hematocrit

Red blood cell count Platelet count

- **Biochemistry:**

Glucose Alanine aminotransferase (ALT)

Urea Gamma‑GT (GGT)

Creatinine Alkaline phosphatase

SodiumTotal Cholesterol

Potassium HDL Cholesterol

Total Bilirubin LDL Cholesterol

Total Protein Triglycerides

Aspartate aminotransferase (AST)

- **Immunology**

CD4/CD8 Index

CD4 / CD8 percentage

CD4 / CD8 count

- **Microbiology**

Viral load

- **Pregnancy test in urine in women**

**Note: Before the beginning of the study, all labs will facilitate to the sponsor and to the investigator a list of the reference normal values of the parameters to evaluate during the study.**

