## 9.3. PROCEDURE FOR REPORTING ADVERSE EVENTS

**The investigator:**

The investigator will immediately notify the study sponsor of any serious and/or unexpected adverse events (see section 9.1.).

The report will be realized during the first 24 hours since the start of the serious adverse event. Notification will be made by means of the adverse events reporting form contained in Appendix V of this protocol. This form will be sent to the sponsor by fax.

Adverse events identified in the course of a clinical trial are to be documented in the database (see Appendix I for CRD content).

All adverse events will be notified in table form in the final report of the clinical trial.

All adverse events will be recorded, regardless of the imputability (i.e., causal) relationship involved, in the corresponding adverse events description form. The latter is found in the CRF of each participant in the study (see Annex I).

Depending on the nature of the condition, each adverse event is to be classified as:

- serious / not serious
- unexpected / expected

The characteristics of the event, its seriousness and "expectability", determine when and how it is to be reported to the health authorities.

The recording of adverse events is the responsibility of the trial investigator team, which should indicate the time of appearance of the event (expressed in the shortest time unit possible), its serious / not serious status, and whether it was expected or unexpected. The intensity of the event (mild, moderate or severe) is to be specified, along with the measures adopted (none, treatment, exclusion), course (complete remission, partial remission, persistence) and imputability based on the criteria indicated in section 9.2.

Intensity will be assessed by the investigator using the following terms according to the OMS criteria:

- Grade I-II
- Grade III-IV

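### No biochemistry or haematology is scheduled between baseline and week 12, so short-lived early laboratory toxicity may be missed by the grade 3 or higher endpoint

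*Protocol*

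**What the plan says.** Section 8.3 sets the calendar: "Study visits would be at entry (BL) and weeks 4, 12, 24, 36 and 48". It then states that "a complete biochemistry and haematology will be performed at every visit", with one exception: "except for week 4 where only CD4 count and viral load will be performed". Biochemistry and haematology are therefore scheduled at baseline and at weeks 12, 24, 36 and 48. Section 8.2.2 lists the analytes and introduces them with "The following parameters will be quantified, as needed".

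These results have a use in the plan. Section 8.1.3 lists, under tolerability and toxicity, "Percentage of patients with toxicity ≥ grade 3". It gives no time window and does not limit the endpoint to laboratory events. Section 12.3 names clinical laboratory tests as an input to the descriptive tolerability analysis of all included patients. Section 9.3 adds a route that does not depend on the laboratory calendar: "All adverse events will be recorded, regardless of the imputability (i.e., causal) relationship involved".

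Section 1.0 describes the study as "Clinical trial including a marketed investigational product under different conditions from the authorised". Only the etravirine group starts a new drug at randomization; controls continue their regimen (5.3, 7.3).

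**The concern.** The weeks just after the switch are when one arm is newly exposed to a drug used outside its authorised conditions, and no safety laboratory test is scheduled then until week 12. Section 12.4 defends the small sample partly on the ground that patients will be closely monitored. The safety procedures in section 6.5 add only viral load testing and a virological stopping rule.

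A silent change in liver enzymes, creatinine or blood count that comes and goes within that window leaves no scheduled trace, so the patient may be counted as free of toxicity of grade 3 or higher. With 20 patients per arm, one patient missed in this way moves the arm's percentage by 1/20 = 5 points. At stake is the sensitivity of one secondary endpoint and of the safety tables. The primary virological endpoint is not affected.

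**Working it through.** The protocol states no figure to reproduce here, so the check is a count of visits and an illustration.

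**Inputs from the protocol.** Post-baseline visits at weeks 4, 12, 24, 36 and 48; biochemistry and haematology at all of them except week 4 (8.3). Follow-up 48 weeks (3.9). Twenty patients per arm (6.4).

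**Count.** Four of the five post-baseline visits carry the panel. The first interval without it is 12 weeks, or 12 × 7 = 84 days, and 12/48 = 25% of follow-up. The later gaps (weeks 12–24, 24–36 and 36–48) are also 12 weeks each.

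**Assumptions for the illustration (not in the protocol).** Onset of an abnormality is uniform over weeks 0 to 12, it lasts d weeks, and it is detected if present on a test day. Visits fall on their nominal weeks.

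**Chance of scheduled detection.**
- Week 12 only: the onset must lie in the last d weeks, so the chance is d/12 for d up to 12.
- Weeks 4 and 12: 2d/12 for d up to 4, then (4 + d)/12 for d from 4 to 8, then 1.

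| Duration d (weeks) | Week 12 only | Weeks 4 and 12 |
|---|---|---|
| 2 | 2/12 = 17% | 4/12 = 33% |
| 4 | 4/12 = 33% | 8/12 = 67% |
| 6 | 6/12 = 50% | 10/12 = 83% |
| 8 | 8/12 = 67% | 12/12 = 100% |
| 12 | 12/12 = 100% | 100% |

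For durations up to 4 weeks the omission halves scheduled detection. At 12 weeks it makes no difference to whether the event is found.

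**Delay for abnormalities that persist.** With week 12 only, the mean delay is 12 − 6 = 6 weeks. With week 4 added, onsets in weeks 0–4 (probability 4/12) wait 2 weeks on average and onsets in weeks 4–12 (probability 8/12) wait 4 weeks: (4/12) × 2 + (8/12) × 4 = 3.3 weeks.

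**Effect on the comparison.** Suppose such events have the same timing and duration in both arms, at most one per patient, with true proportions pE (etravirine) and pC (control), and let s be the chance of detection. The expected observed difference is s × (pE − pC). If pE = pC, nothing is distorted. If pE exceeds pC, the excess shrinks by the factor s, for example to one third when d = 4 and only week 12 is tested. The protocol gives neither proportion, so the size of any such shrinkage cannot be stated.

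**The case against.** The exception is written deliberately, and no readable text contradicts it. The first interval is no longer than the later ones. An abnormality still present at week 12 is caught. Symptomatic events can surface through adverse event recording (9.3) or the follow-up physical examination (8.2.1), and the wording of 8.2.2 may allow unscheduled tests, though it is ambiguous. The safety analysis is descriptive and the trial is a 40-patient pilot. All of this stands, and it limits the point to asymptomatic abnormalities that resolve before week 12 and to later discovery of those that persist.

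Three stronger readings are tempting, and the protocol does not support them.
- A reader might infer that the toxicity endpoint is blind during the first 12 weeks. It is not: sensitivity is reduced, to a degree that depends on duration.
- A reader might infer that the comparison is biased towards etravirine. Both arms share the schedule, so that follows only if early transient events occur mainly in the switched arm. The protocol offers no data on this, and its rationale (4.1) describes etravirine as having low toxicity.
- A reader might infer a conflict with lipid management or the lipid endpoint, because section 7.5 says "the dose of atorvastatin may need to be altered based on clinical response". That is a general interaction comment with no timing attached, and it does not conflict with a week-12 lipid test. The lipid endpoint in 8.1.3 is the change from baseline to week 48, which a week-4 value would not enter.

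**Conclusion.** The point holds as a minor weakness in outcome measurement. By section 8.3, no biochemistry or haematology is scheduled between baseline and week 12. Short, silent laboratory toxicities in that window may be missed by the endpoint on toxicity of grade 3 or higher and by the safety tables. Under the stated assumptions, scheduled detection of 4-week abnormalities is 33% where 67% was available from a visit that already takes blood, and the mean delay for persisting ones is 6 weeks against 3.3. These figures rest on uniform onset and assumed durations; a different onset pattern would change the sizes, but an added test cannot lower detection. How many events would actually be missed is unknown, because the protocol gives no event rate. The primary endpoint and the week-48 changes in lipids, CD4 and CD8 cells, SCORE risk and patient satisfaction are untouched.

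**What to change.** In section 8.3, remove the week-4 exception for safety biochemistry and haematology in both arms, and run these tests from the blood draw already made at that visit for viral load and CD4 count. State that the results count in the endpoint on toxicity of grade 3 or higher (8.1.3) and in the section 12.3 tables. Check the section 8.3 flow chart for consistency; its marks could not be read in the text available for this review, so it may or may not need editing.

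Week-4 lipids, and a fast for them, are not needed for the week-48 lipid endpoint and can be left out. Glucose is also on the biochemistry list, so the amended text should say whether the week-4 sample is taken fasting.

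The cost is up to 40 routine panels (20 + 20 patients, one each), with no extra visit. The change concerns what is measured and counted; it sets no dose or treatment rule.

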**Flow chart of study procedures:**

|  | SCR | BL | Wk 4 | Wk 12 | Wk 24 | Wk 36 | Wk 48 |
| --- | --- | --- | --- | --- | --- | --- | --- |
| Informed consent |  |  |  |  |  |  |  |
| Pregnancy test |  |  |  |  |  |  |  |
| Clinical visit |  |  |  |  |  |  |  |
| HIV1-1 Viral load |  a |  |  |  |  |  |  |
| CD4 cell count |  a |  |  |  |  |  |  |
| Biochemistry (including lipid profile) |  a |  |  |  |  |  |  |
| Haematology |  a |  |  |  |  |  |  |
| Patient’s satisfaction |  |  |  |  |  |  |  |
| SCORE equation (blood pressure) |  |  |  |  |  |  |  |
| Adverse events |  |  |  |  |  |  |  |
| Plasma sample storageb |  |  |  |  |  |  |  |

a A blood test including HIV-1 RNA, CD4+ counts, biochemistry and haematology performed within 3 months previous to the baseline visit will be accepted as screening.

b Genotypic resistance testing will be performed to all participants experiencing virologic failure during the study.

# 9.- ADVERSE EVENTS

## 9.1. DEFINITION

**Adverse event**: (AE) An adverse event is any medical event presented by a patient or clinical research subject administered a pharmaceutical product, and which does not necessarily have a causal relation to the treatment.

**Serious adverse event**: (SAE) A serious adverse event is a medical event classified as such and which, regardless of the dose involved:

- causes patient death,
- produces a life-threatening situation for the patient,
- requires or prolongs hospital admission,
- produces important or persistent incapacitation/handicap, or constitutes a congenital defect or anomaly,
- needs action to prevent any of above situations.

Examples of such events are intensive care in an Emergency Service or in the home in a patient with allergic bronchospasm; blood dyscrasias or seizures not giving rise to hospital admission, or the development of drug dependency or abuse.

**Unexpected adverse event**: (UAE) An adverse event related to the product in investigation the nature or intensity of which does not coincide with the information available on the product administered (Investigator manual in the case of a non-authorized research drug).

## 9.2. DESCRIPTION OF THE IMPUTABILITY CRITERIA

The causal relation will be established according to the algorithm of the Spanish Pharmacovigilance System, which contemplates the following categories:

**Definitive:**

- A plausible time sequence exists in relation to administration of the drug or its plasma or tissue concentrations.
- The observed manifestation coincides with the known adverse reactions profile of the implicated drug.
- The event cannot be explained by the concurrent disease or by other drugs or chemical substances.
- Response to withdrawal must be clinically plausible, i.e., the condition improves on discontinuing administration of the drug.
- A positive response to repeat exposure is observed.

**Probable:**

- A reasonable time sequence exists in relation to administration of the drug.
- The observed manifestation coincides with the known adverse reactions profile of the implicated drug.
- The event is unlikely to be explained by the concurrent disease or by other drugs or chemical substances.
- Response to withdrawal is clinically plausible, i.e., the condition improves on discontinuing administration of the drug.
- No repeat exposure is required to complete this definition.

**Possible:**

- A reasonable time sequence exists in relation to administration of the drug.
- The observed manifestation coincides with the known adverse reactions profile of the implicated drug.
- The event might be attributable to the clinical condition of the patient or to other concomitantly administered drugs or chemical substances.
- Information concerning drug withdrawal may be unavailable or confusing.

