### 8.1.2. Secondary Study Variables

- CD4+/CD8+ T lymphocytes count.
- Genotypic test if virologic failure occurs.
- Lipid profile: total, HDL-, LDL-cholesterol and triglyceride levels
- Administration of lipid-lowering drugs throughout the study (new administrations or the withdrawal of previous lipid-lowering drugs).
- Cardiovascular risk assessed by the SCORE equation
- Patient’s satisfaction assessed using a 100 mm analogue visual scale.
- Adverse events related to antiretroviral treatment (Toxicity)

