**Improbable:**

- A clinical event, including anomalous laboratory test findings, with a time relation to administration of the drug which makes a causal association unlikely, and where other drugs, chemical substances or intercurrent disease afford plausible explanations for the observed event.

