**Unrelated:**

- None of the above criteria are met.

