**The sponsor:**

The sponsor will inform the Spanish Drug Agency (Ministry of Health), the competent authorities of the autonomous region and the Ethics Committees implicated in the clinical trial about any important information of security of the investigational medicinal product.

The sponsor will inform the Spanish Drug Agency (Ministry of Health) of any serious and unexpected adverse events which may be related to the study treatment, when the investigational medicinal product is not marketed. When it is marketed, it will be informed by means of requirements of pharmacovigilance.

The sponsor will inform competent authorities of the implicated autonomous region and the Ethics Committee of any serious and unexpected adverse events which may be related to the study treatment, and that have been happened in patients in its autonomous region.

The deadlines to notify suspect adverse reaction are:

- 15 days
- 7 days if the suspect adverse reaction has resolved in death or has been life-threatening. The information will be completed in 8 further days.

If the notification is sent in electronic form, it is not necessary to notify the competent authorities of the autonomous region.

The sponsor will keep a detailed register of all the adverse events notified by the investigators.

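### Section 9.2 lets an adverse event count as related only if it is already in the drug's known profile, so a reaction of a new nature cannot be classed as related, which contradicts section 9.1

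*Protocol*

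**What the plan says.** Section 9.2 sets out the causality scale and attributes it to the Spanish Pharmacovigilance System algorithm. Section 9.3 tells the investigator to assign imputability by the 9.2 criteria. Definitive, Probable and Possible each contain the same line: "The observed manifestation coincides with the known adverse reactions profile of the implicated drug". Improbable is for an event "with a time relation to administration of the drug which makes a causal association unlikely" and for which other explanations are plausible. Unrelated is the residual category: "None of the above criteria are met".

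Section 9.1 defines an unexpected adverse event as "An adverse event related to the product in investigation the nature or intensity of which does not coincide with the information available" on the product.

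Three other parts of the protocol depend on these terms:

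- Section 9.3 has the investigator notify the sponsor at once of events that are serious, unexpected, or both.
- Section 9.3 has the sponsor inform the regional authorities and the Ethics Committee of "any serious and unexpected adverse events which may be related to the study treatment".
- Section 8.1.2 lists the toxicity variable as "Adverse events related to antiretroviral treatment (Toxicity". Section 8.1.3 builds two endpoints on toxicity: the share of patients with toxicity of grade 3 or above, and the share who withdraw because of toxicity.

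**The concern.** Whether an event is related and whether it was expected are separate questions. Section 9.2 merges them by making prior knowledge of the reaction a condition for every related category. Section 9.1 needs them apart, because it describes an event that is related and yet outside what is known. An investigator who follows 9.2 to the letter cannot produce an event that is unexpected by its nature.

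This matters more here than it would for a drug used within its label. The protocol describes the trial as using a marketed product under conditions different from those authorised. Section 4.1 dates the European approval to September 2008, and section 12.4 gives the lack of data on this strategy as a reason for the pilot. The known profile may not cover the use being studied. Causality is also assigned as events occur, so a later analysis plan could reclassify events for the report but could not repair reporting that was not triggered at the time.

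**Working it through.** No figure is at stake, so the check sets the passages side by side.

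**Step 1: are the lines in each category joint requirements?** The protocol does not say so outright, but two features support it. Probable ends by saying that re-exposure is not needed to complete the definition, which makes sense only if the preceding lines are needed. Also, the profile line is identical in all three related categories and the time line is identical in Probable and Possible, so the categories could not be told apart if any single line were enough.

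**Step 2: run two test events through 9.2.** Both are of a nature not in the known profile.

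- Event A: good timing, no other cause, improvement on withdrawal, recurrence on re-exposure.
- Event B: good timing, another cause possible, information on withdrawal unavailable.

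| Category | Event A | Event B |
|---|---|---|
| Definitive | fails on the profile line alone | fails on the profile line and others |
| Probable | fails on the profile line alone | fails on the profile line and others |
| Possible | fails on the profile line | fails on the profile line alone |
| Improbable | fails: timing supports causation and there is no other explanation | fails: timing supports causation |
| Unrelated | residual | residual |

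The Unrelated line has two readings. If it means that no category above is satisfied, both events are Unrelated. If it means that no single criterion above is satisfied, both events meet the timing criterion, so they are not Unrelated and have no category. On neither reading are they related. Event A carries all the other evidence that the scale asks for in its top category.

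**Step 3: compare with 9.1.** An unexpected event must be "An adverse event related to the product in investigation", and it must be one "the nature or intensity of which does not coincide with the information available on the product administered".

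- New nature: 9.2 denies relatedness, so 9.1 cannot be met. This part of the definition is empty.
- Known nature, unexpected intensity: the profile line can be met, so the event can be Possible, Probable or Definitive and still be unexpected. This part works.

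**Step 4: follow a new-nature event through the rest of the protocol.**

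| Place | Depends on relatedness? | Result |
|---|---|---|
| 9.3, recording of events | no | recorded |
| 9.3, investigator to sponsor, serious | no | notified |
| 9.3, investigator to sponsor, non-serious but unexpected | yes, through 9.1 | not triggered |
| 9.3, sponsor reporting of serious unexpected events that may be related | yes | not triggered if 9.2 decides relatedness |
| 9.3, sponsor reporting of important safety information | no | remains available |
| 8.1.2 and 8.1.3, the two toxicity endpoints | yes, through the 8.1.2 definition | not counted |
| 8.1.3, all withdrawals | no | counted |
| 12.3, adverse-event tables | no | tabulated |

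**Step 5: size.** The protocol gives no rate of etravirine reactions and no share outside the known profile, so an expected number cannot be derived. What can be said is conditional. With 20 patients in an arm, one patient whose only toxicity of grade 3 or above was misclassified in this way would move that arm's percentage by 1/20 = 5 percentage points.

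**The case against.** The strongest reply is that the safety data are protected elsewhere. Section 9.3 records every event whatever its imputability and sends every serious event to the sponsor. The sponsor must also pass on important safety information, with no causality condition. For a marketed product, reporting to the national agency follows pharmacovigilance requirements that the protocol does not reproduce. Section 12.3 tabulates all events. All of this stands. A reader might infer that new etravirine toxicity would go unseen, and the documents do not support that.

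A reader might also infer that no unexpected reaction could ever be classed as related. That is too strong, because section 9.1 also covers unexpected intensity.

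A third reply is that 9.2 was not meant to be applied so rigidly. Parts of Possible are permissive, since information on withdrawal may be missing and another cause might exist. A strict joint reading can leave even some events inside the known profile without a related category, for example a well-timed event with no other cause that does not improve on withdrawal. The parent algorithm may treat unlisted reactions differently, and it cannot be seen here. This shows that 9.2 is loosely drafted. It does not remove the problem, because the profile line is not among the permissive ones and 9.3 names 9.2 as the basis for imputability.

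Finally, the sponsor's trigger of possible relatedness is not tied to a named 9.2 category, and 8.1.3 does not say which categories count as toxicity. Both links are therefore inferred. That is fair, but the protocol offers no other scale by which to decide either question.

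**Conclusion.** The point holds for reactions of a new nature. As written, 9.2 cannot class them as related, which contradicts 9.1 and, read together with 9.2, takes them out of the relatedness-based reporting in 9.3 and the two toxicity endpoints in 8.1.3. The consequence is misclassification, not loss of data.

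The conclusion rests on two assumptions: that the lines within each category are joint requirements, and that 9.2 decides what counts as related in 9.3 and 8.1.2.

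Two further inferences are tempting and are not supported. One is that the filter biases the toxicity comparison towards etravirine because control patients already tolerate their protease inhibitor. The inclusion criteria in section 6.2 admit patients because of dyslipidaemia, gastrointestinal disturbance or dissatisfaction with their current regimen, and nothing in the protocol fixes a direction of bias. The other is a numerical estimate of how far toxicity is understated, for which the protocol gives no inputs.

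This is a 40-patient pilot with toxicity under a secondary objective and a descriptive adverse-event analysis. The wording should be corrected, preferably before enrolment, but it does not threaten the trial.

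**What to change.** Reconcile 9.2 with 9.1, 9.3 and 8.1.2:

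- In Possible, remove agreement with the known profile as a requirement.
- In Probable and Definitive, make it supporting evidence instead of a condition.
- Say explicitly that a reasonably timed event of a new nature can be at least Possible.
- Keep expectedness as the separate classification already in 9.1 and 9.3.
- In 8.1.2 or 8.1.3, state which 9.2 categories count as toxicity.
- Carry the same wording to the adverse-event form in the CRF.

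If the sponsor wants to keep the cited algorithm's categories unchanged, the protocol should state how an unlisted reaction is handled under it, so that 9.1 and 9.2 agree.

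The cost is about a paragraph of protocol text with the matching CRF wording, and somewhat more events classed as possible and reported. Treatment, sample size and visit schedule do not change.
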